#### Pain at other sites (hips, knees, ankles, other foot sites, spine)

This is scored as the number of other pain sites, and severity of pain at each site using NRSs described above (terminal descriptors ‘no pain’ (score = 0) and ‘worst pain possible’ (score = 10)).

#### Treatment adherence

Participants record the hours/day they wore their orthoses/insoles and footwear daily for the final 7 consecutive days of weeks 4, 8 and 12 in log books. Adherence will be calculated as the average percentage of time spent wearing the study orthoses/insoles when wearing shoes. Participants will be classified as adherent if they wear their insoles for an average of at least 70% of the time spent wearing shoes. Participants in both groups also rate their adherence to wearing their allocated insoles using an 11-point NRS (from ‘not at all’ (score = 0) to ‘completely as instructed’ (score = 10)) at the 12-week follow-up. Finally, participants also indicate if they ceased wearing their study insoles over the course of the study on a categorical scale (yes or no) at the 12-week follow-up. Those who respond ‘yes’ are required to describe why and when they ceased wearing their allocated insoles, and this information will be reported descriptively.

#### Descriptive measures

Descriptive measures are assessed at baseline unless otherwise indicated. These include age, height, weight, body mass index, gender, duration of symptoms, current employment status and expectation of treatment outcome (assessed on a 5-point ordinal scale from “no effect at all” to “complete recovery”). Credibility of the allocated insole is assessed via the Credibility/Expectancy Questionnaire (CEQ) [37] during the clinic visit immediately after receiving the allocated insole. First MTP joint radiographic disease severity is measured during radiographic screening using a validated atlas [23].

#### Clinical data

At the initial clinical visit, the podiatrist assesses foot posture with the participant standing barefoot using the foot posture index (FPI) [29]. The FPI is scored between − 12 (severely supinated) to + 12 (severely pronated). The number and proportion of participants with a supinated (− 12 to − 1), neutral (0 to + 5) or pronated (scores of + 6 to + 12) foot posture will be reported. Hallux valgus severity is assessed using the Manchester scale [24]. Big toe joint dorsiflexion range of motion is measured with the participant in supine using a goniometer [38]. Orthoses modifications (e.g. use of a first ray cut out/extension and/or varus wedge) and footwear type and/or advice are documented using a custom table at the initial clinical visit.

### Sample size calculations

The minimal clinically important difference (MCID) in our primary outcome is a change in NRS walking pain of 1.8 out of 10 units [39]. We assume a between-participant standard deviation of 2.5 and a baseline to 12-week correlation of 0.3 using our pilot RCT data. Using ANCOVA adjusted for baseline score, we need 37 participants per arm to achieve 90% power to detect the MCID in pain. Therefore, we will recruit 44 people per arm in total (*n* = 88) to allow for 15% attrition. We have not adjusted the sample size for clustering because podiatrists treat a similar proportion of participants from each group.

### Statistical analyses

A study biostatistician blinded to group allocation will analyse the data. Main comparative analyses between groups will be conducted using intention-to-treat. We will use multiple imputation if > 5% of primary outcome data is missing. To assess whether insole group influences change in walking pain, differences in mean change in pain (baseline minus follow-up) will be compared between groups using linear regression models adjusted for baseline scores on the NRS walking pain, and the stratifying variable of podiatrist. Analyses for continuous secondary outcomes will be conducted similarly. Between-group improvements in participant-perceived global change will be compared using risk differences, calculated from binomial regression models with a logarithmic link, adjusting for the stratifying variable of podiatrist. If this model fails to converge, logistic regression models will be fit. Complete-case analyses will also be conducted. A sensitivity analysis will be undertaken to investigate the effects of insoles assuming full adherence (defined as 70% of time when shod, based on log book data), using an instrumental variables approach [40].

To explore if the effect of insole group on NRS walking pain is moderated by i) BMI, ii) a composite score for osteophyte or joint space narrowing, or iii) first MTP joint range of motion, interaction terms between insole group and each of these variable will be independently included in regression models for NRS walking pain.

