### Randomisation, blinding and allocation concealment

Participants are randomised to either the contoured foot orthoses group or the sham flat insoles group using a randomisation schedule prepared by the study biostatistician. Randomisation occurs on a 1:1 allocation with permuted block sizes of 6 to 12, stratified by podiatrist/clinic. The schedule is uploaded and stored on a password-protected website (REDCap) where access is limited to a researcher not involved with participant recruitment or outcome measure administration to ensure concealment. Group allocation is revealed by a different researcher not involved in either participant recruitment or data collection after baseline outcomes have been completed.

Limited disclosure is used to blind participants to group allocation. Participants are told that this clinical trial is comparing two types of insoles but they are not informed about the characteristics of the insoles provided to either group, consistent with our previous insole and footwear OA trials [25, 26]. Participants are also not informed about the specific aims or hypotheses of the study until after the study is completed. At this time, participants will be given a summary outlining the study purpose and main findings. Primary and secondary outcomes are participant-reported, thus this study is also assessor-blinded (because participants are blinded). Study researchers entering participant-reported data will be blinded, as will the study biostatistician performing the statistical analyses. The podiatrists administering the insoles will not be blinded, which is a recognised difficulty when conducting trials using a physical intervention [27]. Stratification by podiatrists/clinics will ensure each podiatrist will treat a similar proportion of participants in both groups to ensure that the effects of podiatrist personality on the therapeutic alliance are consistent across groups.

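### The participant-perceived change ratings are adjusted for podiatrist only, which may give up some precision (without bias), and the stated models do not directly give the stated risk difference

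*Protocol article*

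**What the plan says.** The Statistical analyses section compares the primary outcome by "linear regression models adjusted for baseline scores on the NRS walking pain, and the stratifying variable of podiatrist", and treats continuous secondary outcomes in the same way. Risk differences for the participant-perceived change ratings are to be "calculated from binomial regression models with a logarithmic link, adjusting for the stratifying variable of podiatrist", with logistic regression if that model does not converge. Podiatrist is therefore the only covariate named for these ratings.

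Under Participant-perceived change, pain, function and overall status are each rated once, at 12 weeks, as change since baseline. A participant counts as improved in the top two of the seven categories. The ratings have no baseline value of their own. Under Procedure, allocation takes place only after the baseline questionnaire is returned, so baseline walking pain is known for everyone randomised.

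**The concern.** A covariate need not be the outcome's own baseline to be useful; it only has to predict the outcome. Starting pain is a natural candidate for a rating of change in pain, because it limits how far a person can improve. Leaving it out may make these risk differences less precise than the same data allow, in a trial of 88 people sized only for the walking-pain scale.

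The second issue is the effect measure. The plan names a risk difference, but the models it names work on other scales. Unless the conversion is stated, the reported measure could depend on whether the first model converges.

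**Working it through.** **The plan's own figure.** The Sample size calculations section takes the target difference as "a change in NRS walking pain of 1.8 out of 10 units" and assumes a "between-participant standard deviation of 2.5 and a baseline to 12-week correlation of 0.3". With two-sided alpha of 0.05 (my assumption):

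- adjusted SD = 2.5 × √(1 − 0.3²) = 2.385
- n per arm = 2 × [2.385 × (1.960 + 1.282) / 1.8]² = 36.9, so 37
- with attrition: 37 / 0.85 = 43.5, so 44 per arm and 88 in total

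The stated size reproduces. It concerns walking pain; the article gives no figure for the ratings.

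**How strongly might baseline pain predict perceived change?** Suppose the rating follows change in walking pain (baseline minus follow-up). With follow-up SD 2.5 and correlation 0.3,

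corr(baseline, change) = (s − 0.3 × 2.5) / √(s² + 2.5² − 2 × 0.3 × s × 2.5), where s is the baseline SD.

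- s = 2.5: 1.75 / √8.75 = 0.59
- s = 2.0: 1.25 / √7.25 = 0.46
- s = 1.5: 0.75 / √6.25 = 0.30

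The article does not give the baseline SD separately. The Participants section requires a walking-pain score of at least 3, so baseline runs from 3 to 10. Even an even spread over those eight scores has SD √((8² − 1)/12) = 2.29. A baseline SD of 2.5 is therefore at the high end, and 1.5 to 2.5 is the range I assume.

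**Precision against a plain difference in proportions.** These are simulations with 20,000 trials per scenario, 37 per arm, linear adjustment on the risk-difference scale and podiatrist left out. The s = 2.5 rows assume a true pain difference of 1.0 and 35% improved with sham.

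| Rating follows | Baseline SD | Change in variance from adding baseline pain |
|---|---|---|
| Change in pain | 2.5 | 20% cut |
| Change in pain plus noise (SD 1.5) | 2.5 | 16% cut |
| Change in pain | 2.0 | 9–13% cut |
| Change in pain | 1.5 | 3–4% cut |
| 12-week pain only | 2.5 | 3–4% cut |
| Halfway between the two | 2.5 | 1% cut |
| Halfway between the two | 1.5 or 2.0 | no gain, about 1% worse |

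**Precision against the model actually planned.** With eight podiatrists (Insole interventions section) already in the model, 37 per arm and baseline SD 1.5 to 2.5, the variance changes by between about a 2% increase and a 21% cut. In standard-error terms this is from √1.02 = 1.01 to √0.79 = 0.89 times the planned value.

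**Validity without baseline pain.** In a separate simulation with 37 per arm, 30% improved with sham, 30% or 60% with orthoses, and latent baseline–outcome correlations from 0 to 0.5, the mean unadjusted risk difference was about 0.00 or 0.30, as it should be. Coverage of the nominal 95% interval was 94.1% to 94.9%.

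**Chance imbalance.** One standard error of the baseline difference is 2.5 × √(2/37) = 0.58 points. Such an imbalance moves the unadjusted risk difference by about 5 percentage points if ratings follow change, and by 2 to 3 points in the opposite direction if they follow current pain. The standard error is about 11 points.

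**Effect measure.** Take 30% improved with sham and 60% with orthoses, both assumed. A log-link coefficient returns 0.60/0.30 = 2.0, and a logistic coefficient returns (0.60/0.40)/(0.30/0.70) = 3.5. The risk difference is 0.30. A common risk ratio of 2.0 implies a difference of 0.20 where the sham risk is 20% and 0.40 where it is 40%, so with podiatrist in the model an averaging step is needed.

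**The case against.** The plan follows a coherent rule: adjust for an outcome's own baseline where it has one, and always for the randomisation stratifier. Of the randomisation the article states: "Randomisation occurs on a 1:1 allocation with permuted block sizes of 6 to 12, stratified by podiatrist/clinic". The ratings have no baseline score, so podiatrist alone is a recognised choice. This stands, and the plan does not contradict itself.

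The documents also do not show that baseline pain predicts these ratings. The correlation of 0.3 is between walking-pain scores at two times. Even the direction of the association depends on what participants have in mind when they rate, and in the halfway case the gain vanishes. This stands too, and is why precision may be lost rather than will be lost. The choice of covariate also involves judgement: baseline function could be argued for the function rating. Walking pain has the merit of being the primary outcome's baseline.

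A continuous covariate strains a log-binomial model that already carries eight podiatrists with about 74 people analysed. That is true if the log link is kept; standardising from a logistic model largely avoids it.

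On the effect measure, the article says the risk differences are calculated from the models, so a conversion may be intended and may be written in a fuller plan that is not shown. The point is only that neither named model gives a risk difference directly.

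**Conclusion.** The point holds as a cheap possible gain in precision for secondary outcomes, together with a mismatch between the named models and the named measure. Its size against the planned model runs from about a 2% increase to a 21% cut in the variance of the risk difference. It rests on 37 analysed per arm, follow-up SD 2.5, correlation 0.3, an assumed baseline SD of 1.5 to 2.5, and an unknown link between the ratings and pain. The upper end needs both a baseline SD of 2.5 and ratings that follow change in pain.

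A reader might infer that chance imbalance in baseline pain biases these comparisons, or that disagreement with the primary result would show a flaw. The documents do not support that. Under randomisation such imbalance is ordinary sampling error, and the confidence interval covers it at close to its nominal level. Nor do they support the firm claim that precision will be lost, or that a cut of about a fifth is the expected gain.

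**What to change.** In the Statistical analyses section, name continuous baseline NRS walking pain next to podiatrist as a covariate for all three participant-perceived change ratings. State that the risk difference is obtained by marginal standardisation over the observed baseline pain and podiatrist distribution, for example from a logistic model, and that this applies whichever link is used. The reported measure then does not depend on convergence.

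This should be fixed before allocation is revealed to the analyst. The Timelines section describes recruitment as suspended and still to recommence, so there was time when the article was written. The cost is a sentence or two of wording and one degree of freedom, with no new data. If baseline pain is unrelated to the ratings, the loss is negligible: the simulated standard deviation of the risk difference goes from 0.106 to 0.107. Convergence becomes harder only if the log link is kept.

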### Timelines

The institutional Human Research Ethics Committee approved the study in June 2019. We started participant recruitment in August 2019 and intended to complete recruitment by May 2020. However, due to the outbreak of the COVID-19 virus, recruitment was suspended in March 2020. Final 12-week follow-up data collection was expected to be completed by August 2020, but this will be revised upon recommencement of recruitment.

## Discussion

This protocol outlines the first RCT comparing the effects of contoured foot orthoses to sham flat insoles on pain and other symptoms in people with first MTP joint OA. Foot orthoses are a promising intervention for people with first MTP joint OA. They have been found to alter the biomechanical function of the first MTP joint and foot, and these biomechanical changes are associated with a reduction in joint pain [14–18]. Furthermore, foot orthoses are already widely used by allied health clinicians such as podiatrists and physiotherapists [20], and adherence to their use is good [9], thus our trial reflects current clinical practice. Foot orthoses are also relatively inexpensive, and our study protocol only requires two clinical visits, so the overall cost of our intervention is modest.

Unlike for hip and knee OA, there are no “joint-specific” clinical guidelines for managing patients with first MTP joint OA, and scant research is available to guide clinical practice. Outcomes from our clinical trial will provide much needed evidence regarding a common biomechanical intervention currently used to manage symptoms in people with first MTP joint OA. This information will assist clinicians treating people with this condition, and may be used in future clinical guidelines for this under-researched patient cohort.

## Data Availability

The datasets used and/or analysed during the current study will be made available from the corresponding author on reasonable request.

## Abbreviations

AQoL: Assessment of Quality of Life
CONSORT: Consolidated Standards of Reporting Trials
FPI: Foot posture index
HREC: Human Research Ethics Committee
NRS: Numerical rating scale
OA: Osteoarthritis
PASE: Physical Activity Scale for the Elderly
RCT: Randomised controlled trial
SPIRIT: Standard Protocol Items: Recommendations for Intervention Trials
